#### **Primary H1**

Patients assigned to BI/RT+ will attend more substance intervention and community-based specialty treatment sessions outside of the FQHC over the 12-month follow-up than patients assigned to BI/RT.

A linear mixed effects model [57] will be used to compare participants in the two groups on the number of sessions attended in the past 90 days at the 3-, 6-, 9-, and 12-months follow-up assessments. The model will include terms for intervention group, drug type (i.e., illicit drug or alcohol/marijuana), time, BHC/site, and relevant interactions along with any necessary covariates. For these analyses we will combine alcohol and marijuana use given the high prevalence of co-occurring use as well as the social acceptability and decriminalized status of marijuana in Philadelphia, which can contribute to a decreased perception for need for treatment. Specific contrasts will compare (1) differences between individuals in the illicit drug sub-group who received the BI/RT intervention and those who received the BI/RT+ intervention and (2) differences between individuals in the alcohol/marijuana sub-group who received the BI/RT intervention and those who received the BI/RT+ intervention. The mixed effects model will be performed using SAS’s PROC MIXED.

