**Aim 1:** To conduct a randomized controlled trial to address the following ***Primary Hypotheses***:

### **H1**

Patients assigned to BI/RT+ will attend more substance intervention and specialty treatment sessions outside of the FQHC over the 12-month follow-up than patients assigned to BI/RT.

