#### BI/RT

Participants in the BI/RT condition attended one 20–40 min audio-taped brief intervention session with the BHC that was intended to approximate standard SBIRT delivered by a BHC in a FQHC setting. This session occurred at the primary care site on the same day that the participant enrolled into the study. The BHC employed motivational interviewing techniques (MI; [49]) to explore the patients’ perceptions of their substance use. Exploring a referral to treatment was a standard component that was provided as part of the BI/RT intervention; the type of referral that was made depended on the severity of the patient’s substance use. Patients with scores indicating they have “mild” severity (occasional risky/illicit use) were encouraged to curtail illicit drug use and reduce alcohol use. Patients with scores in the “moderate” range were referred to brief treatment resources and self-help resources in the community. Patients whose scores on the screening instruments placed them in the “severe” range were referred to specialty care in the community. Level of specialty care referral (e.g., detoxification, residential, intensive outpatient) was determined based on degree of physical dependence symptoms that the patient disclosed.

The BHC followed up the initial brief intervention with a telephone call 3–4 weeks after the session. This call was intended to review the patient’s efforts to make reductions in substance use, as well as efforts to engage in 12-step recovery meetings or to follow up on treatment referrals. If necessary, the BHC offered alternate treatment referrals and/or resources.

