#### BI/RT+

Participants in the BI/RT+ condition attended 2–6 (20–40 min each) audio-taped sessions that were intended to approximate the provision of severity-appropriate expanded brief intervention. The first session occurred at the primary care site on the same day that the participant enrolled into the study, and subsequent sessions occurred at the primary care site within the following 12 weeks. Similar to the BI/RT condition, the BHC employed MI techniques to explore the patient’s perspective on their substance use. However, the BHC modeled their motivational techniques after the Motivational Enhancement Therapy (MET) approach employed in Project Match [26]. This approach spreads brief intervention over sessions, allowing the BHC more time to negotiate a change plan with the patient. In addition, the BHC had numerous tools, described in more detail below, that they could employ over these multiple brief intervention sessions to assist patients in achieving their goals. Just as in the BI/RT condition, exploring a referral to treatment was a standard component of BI/RT+. Patients with scores in the “mild” and “moderate” severity range received MET geared towards helping them set a reduction or abstinence goal and a strategy for following up on this goal. “Mild” and “moderate” severity patients were generally not referred out to community counseling resources, rather they were offered up to six sessions of brief intervention that incorporated cognitive-behavioral strategies or 12-Step facilitation strategies to assist them in pursuing their reduction or abstinence goals. Patients who screened in the “severe” problem range were typically referred out to specialty care. However, the BHC was instructed to utilize repeated sessions of brief intervention to resolve treatment entry barriers with patients. Furthermore, after referred patients connected with specialty care, the BHC could offer 1–2 interventions to process patient reaction to the treatment experience and augment motivation to remain in specialty care.

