### Patient follow-up procedures and outcome measures

Patients in both the BI/RT and BI/RT+ conditions were asked to complete follow-up assessments every 3 months following baseline for 1 year (i.e., at 3, 6, 9, and 12 months post-recruitment). Assessments took place in person, generally at the health center where the patient was recruited.

Table 2 provides a summary of each of the variables involved in the trial and indicates the relevant purpose of the variable, the instrument used to assess that variable, and the assessment points where the instrument was delivered.

**Table 2 Tab2:** Outcome variables and assessment points

Variable	Purpose	Instrument	Assessment points
Drug and alcohol problems	Screen, randomize	AUDIT, DAST-10	Screening
Intervention and treatment engagement	Hypothesis 1	NSMOS, patient charts	Baseline, 3-, 6-, 9-, 12-months
Drug use and severity	Hypothesis 2	ASI, urinalysis, MINI	Baseline, 3-, 6-, 9-, 12-months
Medical and psychosocial functioning and HIV risk	Hypothesis 3	ASI, HIV-RA, chronic conditions Questionnaire, healthy days	Baseline, 3-, 6-, 9-, 12-months
Readiness to change and personal stress	Covariates	Personal rules, PSS-4	Baseline, 3-, 6-, 9-, 12-months
Patient satisfaction	Evaluation	Client satisfaction form	3-months

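### H1 counts sessions outside the FQHC, but the arms refer moderate-severity patients differently and the H1 contrasts pool over severity, so the result may be diluted and is hard to interpret

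*Protocol article*

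**What the plan says.** **Endpoint.** The aims state H1 as BI/RT+ patients expected to "attend more substance intervention and specialty treatment sessions outside of the FQHC over the 12-month follow-up". The Data analysis section repeats this as "will attend more substance intervention and community-based specialty treatment sessions outside of the FQHC over the 12-month follow-up". Table 2 gives the H1 source as "NSMOS, patient charts".

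**Referral rules in BI/RT.** Mild patients "were encouraged to curtail illicit drug use and reduce alcohol use". Those in the moderate "range were referred to brief treatment resources and self-help resources in the community". Severe patients are referred to community specialty care.

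**Referral rules in BI/RT+.** Mild and moderate "severity patients were generally not referred out to community counseling resources, rather they were offered up to six sessions of brief intervention". The sessions are in-house: "subsequent sessions occurred at the primary care site within the following 12 weeks". Severe patients are typically referred to specialty care, and further sessions are used to work on barriers to entry and on staying in treatment.

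**Analysis.** The H1 model names intervention group, drug type, time and BHC/site, plus interactions and covariates that are not specified. The two planned contrasts compare the arms within illicit drug users and within alcohol/marijuana users. Severity (mild, moderate, severe) is a randomisation stratifier, chosen because it is held to moderate the effect of brief intervention, but it is not among the named H1 model terms and no contrast by severity is listed.

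**The concern.** In the moderate stratum, delivery exactly as planned tends to raise the outside-session count in the control arm and to replace outside sessions with in-house ones in the experimental arm. In the severe stratum, BI/RT+ is meant to raise the same count. H1 therefore measures two different things in two strata, possibly with opposite signs, and each planned contrast averages over them.

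A null or negative H1 could then mean that BI/RT+ failed to improve engagement, or that in-house care stood in for outside care as intended. The pooled contrast cannot tell these apart. H1 is a primary hypothesis tested at one quarter of the overall alpha.

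**Working it through.** **1. The rules side by side**

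| Severity | BI/RT | BI/RT+ | Expected effect of BI/RT+ on outside sessions |
|---|---|---|---|
| Mild | Advice to cut down | In-house sessions, as a rule no outside referral | About none |
| Moderate | Referred to community brief treatment and self-help | In-house sessions, as a rule no outside referral | Down, if BI/RT referrals are taken up |
| Severe | Referred to specialty care | Typically referred to specialty care, plus sessions to aid entry and retention | Up, as H1 intends |

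**2. The plan's own power figure.** Inputs from the power section: two-sided alpha .05/4 = .0125, correlation .5, 20% attrition. I take the mean of four follow-ups, whose SD is sqrt((1 + 3 × .5)/4) = 0.791 of the single-visit SD.

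- Alcohol/marijuana: 200 × 0.8 = 160 per arm. d = .30 gives 81.5% power; the d detectable with 80% power is .295. The stated 80% is reproduced at the upper end of the stated range (.25 to .30). d = .25 gives 63.0%.
- Illicit drugs: 100 × 0.8 = 80 per arm. d = .5 gives 93.3%, so the stated 80% is conservative.

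These figures concern one average effect per drug-type contrast. They make no allowance for opposing effects inside it.

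**3. The pooled H1 difference.** With mild taken as zero,

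difference (BI/RT+ minus BI/RT) = p_severe × gain_severe − p_moderate × loss_moderate.

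The shares are those within the contrast concerned. The sign reverses when gain_severe / loss_moderate < p_moderate / p_severe.

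**4. Range.** The article gives neither severity shares nor attendance, so all values here are assumptions: a loss of 1.5 outside sessions per 90 days in moderate patients and a gain of 0.5 to 3 in severe patients.

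| Moderate / severe share | At gain 0.5 | At gain 3 |
|---|---|---|
| 20% / 60% | .6 × 0.5 − .2 × 1.5 = 0.0 | .6 × 3 − .2 × 1.5 = +1.5 |
| 40% / 40% | .4 × 0.5 − .4 × 1.5 = −0.4 | .4 × 3 − .4 × 1.5 = +0.6 |
| 50% / 30% | .3 × 0.5 − .5 × 1.5 = −0.6 | .3 × 3 − .5 × 1.5 = +0.15 |
| 60% / 20% | .2 × 0.5 − .6 × 1.5 = −0.8 | .2 × 3 − .6 × 1.5 = −0.3 |

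Dilution without reversal: at 40% / 40% with a severe gain of 2, the severe stratum contributes .4 × 2 = 0.8 and the moderate stratum takes away .4 × 1.5 = 0.6, which leaves 0.2.

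A smaller moderate loss removes the reversal. With a gain of 3 and a loss of 0.5, 20% severe and 50% moderate give .2 × 3 − .5 × 0.5 = +0.35.

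**The case against.** **The moderate loss may be small.** The BI/RT+ rule is not absolute: it says that mild and moderate "severity patients were generally not referred out to community counseling resources". Exploring a referral is a standard part of both arms. BI/RT+ can include 12-Step facilitation, which may raise outside self-help attendance, and its telephone monitoring can lead to new referrals. The article's background also reports little evidence that SBIRT referral raises specialty treatment engagement. All of this stands. It limits the size of the opposing effect but does not remove the difference in referral rules.

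**A reader might infer that H1 runs against BI/RT+ as a whole, or will reverse.** The document does not support that. One stratum of three is affected, and a reversal depends on shares and attendance that are not given.

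**A reader might also infer that in-house sessions count, so that BI/RT+ wins by design.** Two to six sessions against one would be a built-in lead of 1 to 5. Table 2 lists patient charts, and the abstract omits the words on location. But both statements of H1 place the sessions outside the FQHC, and the NSMOS is by name and description a record of non-study services. That reading is unlikely, and one clarifying sentence settles it.

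**The unseen analysis plan may add severity.** The model does allow unspecified interactions and covariates. But the article fixes the H1 contrasts, and they are by drug type. A severity covariate alone would leave their pooled meaning unchanged.

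**Other primary outcomes cover benefit.** Urine results, days of use and net benefit do bear on whether BI/RT+ works. They do not tell a reader what H1 itself shows.

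**Conclusion.** The concern holds in a limited form. H1 and the referral rules are partly at odds: the rules work against H1 in moderate patients, with it in severe patients, and roughly neutrally in mild patients. The planned contrasts pool these strata. The pooled difference can be diluted, and it reverses only if the severe gain divided by the moderate loss is below the moderate share divided by the severe share. On the assumed values above it runs from −0.8 to +1.5 sessions per 90 days. The signs of the stratum effects follow from the text; their sizes do not.

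It might seem to follow that the confirmatory H1 test should move to the severe stratum. That does not hold up. At an assumed severe share of 20 to 40% there are 60 to 120 severe patients per arm, or 48 to 96 after 20% attrition. The detectable d is then 0.791 × sqrt(2/48) × 3.339 = .54 down to 0.791 × sqrt(2/96) × 3.339 = .38 (3.339 is the sum of the normal quantiles for two-sided alpha .0125 and 80% power), against .295 in the alcohol/marijuana contrast. Recruitment is complete and participants, BHCs and research assistants are unblinded, so narrowing a primary hypothesis to the stratum most likely to favour BI/RT+ would itself invite doubt.

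**What to change.** - Keep the two planned H1 contrasts by drug type as primary.
- Add severity, already a randomisation stratifier, and an arm-by-severity term to the H1 model. Average the primary contrasts over severity at the observed shares, so that they keep their planned meaning.
- Report the BI/RT+ v BI/RT difference within mild, moderate and severe as prespecified supporting contrasts. Interpret the moderate stratum as possible substitution of in-house for outside care.
- State that the H1 count is community and specialty sessions outside the FQHC, and that study BHC sessions and calls are excluded. Report in-house sessions separately, as exposure.

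This should be fixed in writing before H1 is analysed. It uses data already collected and leaves the referral rules unaltered. The cost is a little more analysis, and by-severity estimates that are less precise than the powered contrasts (detectable d of about .38 to .54 in severe patients at the assumed shares), so they support interpretation and are not confirmatory tests.

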### Data analysis

A total of 600 patients were randomized to the BI/RT or BI/RT+ conditions, and we stratified based on site, behavioral health consultant, and drug or alcohol severity (mild, moderate, or severe based on AUDIT or DAST-10 score). These stratification variables were chosen to account for possible differences in intervention delivery and treatment response. Specifically, we aimed to account for general site differences such as neighborhood/population served, typical amount of clinical contact received by patients, and range of services available. Similarly, we chose to stratify randomization by BHC in order to equalize non-specific provider variables across conditions. Because severity of substance use has consistently been demonstrated to moderate the impact of brief intervention on substance use [13], we equalized the proportion of mild, moderate, and severe substance use across conditions. Prior to performing all analyses, standard data screening/cleaning procedures will be applied. These procedures will (1) re-screen the data for data-entry errors, (2) check for outliers, (3) assess the extent and pattern of missing data, and (4) check that appropriate assumptions of normality are met and employ remedial measures such as power transformations whenever necessary. The randomization will be checked by comparing the groups on relevant background variables and on all baseline dependent measures. The comparisons will use analyses of variance for continuous variables and log-linear models for discrete or ordinal responses. Some covariates will be considered for inclusion in the main analyses to improve the precision of our hypothesis testing [56]. In addition, we have powered the study sufficiently to conduct subgroup analyses. Based on the literature, it is possible that patients who are using harder illicit drugs (cocaine, heroin, etc.) may respond differently to BI/RT and BI/RT+ than patients who are only using marijuana, or who use marijuana but primarily have a problem with alcohol. We will be adequately powered to break out these subgroups for secondary analysis. Below we specify each hypothesis and discuss the statistical procedures we will employ in analyzing the data.

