#### **Primary H2**

Patients assigned to BI/RT+ will demonstrate larger reductions in drug use by point prevalence urine samples and by reported days using over the 12-month follow-up compared to patients in BI/RT.

A generalized estimating equations (GEE) model [58] will be used to compare participants in the two groups on rate of urine-confirmed drug abstinence at each follow-up assessment, and linear mixed effects models will be used to examine days of self-reported drug use in the past 30 days at each follow-up assessment. The models will be similar to those outlined for H1, and the baseline response variable (i.e., urine result or days drug use) will be entered as a covariate in the model. As with H1, contrasts will examine the effects of the intervention separately for the two drug type sub-groups. Analyses will be performed using SAS’s PROC GENMOD (GEE) and PROC MIXED.

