#### **Secondary H4**

Patients assigned to BI/RT+ will demonstrate better medical, employment, legal, and psychiatric functioning, as well as reduced HIV risk over the 12-month follow-up compared to patients in BI/RT.

Linear mixed effects models will be used to compare participants in the two groups on measures of psychosocial functioning as assessed by the standard summary scores of the ASI (Medical, Employment, Legal, and Psychiatric) at each follow-up assessment. We will also calculate an overall HIV risk score as assessed by the HIV-RA at each follow-up point. The models will be similar to those outlined for H1, and the baseline response variable will be entered as a covariate in the model. As with H1, contrasts will examine the effects of the intervention separately for the two drug type sub-groups.

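### H1 is the only mixed-model outcome whose baseline value is not a prespecified covariate, although its instruments are scheduled at baseline

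*Protocol article*

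**What the plan says.** - **H1 (Data analysis, Primary H1).** A linear mixed model is fitted to the "number of sessions attended in the past 90 days at the 3-, 6-, 9-, and 12-months follow-up assessments". Its terms are intervention group, drug type, "time, BHC/site, and relevant interactions along with any necessary covariates". Baseline sessions are not named.
- **H2 (Data analysis, Primary H2).** The models follow the H1 form, and "the baseline response variable (i.e., urine result or days drug use) will be entered as a covariate in the model".
- **H4 (Data analysis, Secondary H4).** "The models will be similar to those outlined for H1, and the baseline response variable will be entered as a covariate in the model".
- **H3** is a test on costs and benefits, not a mixed model, so it is outside this comparison.
- **Table 2 (Patient follow-up procedures and outcome measures).** The Hypothesis 1 row gives the instruments as "NSMOS, patient charts" and the assessment points as "Baseline, 3-, 6-, 9-, 12-months".
- **Data analysis, opening paragraph.** The groups are to be compared on background variables and on the baseline values of the outcomes. The text then adds: "Some covariates will be considered for inclusion in the main analyses to improve the precision of our hypothesis testing". No covariate is named there.

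**The concern.** The article settles baseline adjustment outcome by outcome. It fixes it for H2 and H4, as an addition to the H1-type model, and leaves it open for H1 without giving a reason. Two things follow.

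First, earlier use of treatment services may predict later use. If it does, leaving it out makes the H1 contrasts less precise than they need to be.

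Second, an open clause combined with a prior look at baseline differences allows the covariate to be chosen after the imbalance has been seen. H1 is a primary hypothesis tested at a Bonferroni-adjusted level, and that choice is better closed in advance, as it is for H2.

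**Working it through.** **Inputs from the article (Power for the primary hypotheses).** Two-sided alpha .05/4 = .0125; correlation .5 between repeated measurements; 20% attrition by month 12; 100 per condition (illicit drug) with d = .5; 200 per condition (alcohol/marijuana) with d = .25–.30; 80% power.

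**Assumptions.** Compound symmetry over the four follow-ups, equal variances, and the same correlation r between baseline and each follow-up. The article does not give r, so it is varied. Attrition is taken at its month-12 level throughout (160 and 80 per arm), which is cautious.

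**Step 1: reproduce the stated power without a baseline covariate.**

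Variance factor of the four-visit mean = (1 + 3 × .5)/4 = .625.

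Detectable d = (2.498 + .842) × √(2 × .625/n).

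- Alcohol/marijuana: n = 200 gives .264 and n = 160 gives .295. Power at d = .30 with 160 per arm is 81.5%. The stated .25–.30 is reproduced.
- Illicit drug: power at d = .5 is 93.3% with 80 per arm and 97.6% with 100, so the stated 80% is conservative.

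The planned mixed-model power therefore does not depend on baseline adjustment.

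**Step 2: add the baseline covariate.**

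The covariance of baseline with the four-visit mean is r, so the adjusted variance factor is .625 − r².

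| r | Variance factor | Variance reduction | Detectable d, 160 per arm | Power at d = .30, 160 per arm | Detectable d, 80 per arm |
|---|---|---|---|---|---|
| 0 | .625 | 0 | .295 | 81.5% | .417 |
| .1 | .615 | 1.6% | .293 | 82.2% | .414 |
| .2 | .585 | 6.4% | .286 | 84.4% | .404 |
| .3 | .535 | 14.4% | .273 | 87.9% | .386 |
| .4 | .465 | 25.6% | .255 | 92.5% | .360 |
| .5 | .375 | 40.0% | .229 | 97.0% | .323 |

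In sample-size terms, r = .2 is worth about 7% more patients (1/.936 = 1.068) and r = .3 about 17% (1/.856 = 1.168).

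**Step 3: chance baseline imbalance.**

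The SD of a chance difference between arms at baseline is √(2/n): .10 SD at 200 per arm and .14 at 100. It passes into the unadjusted follow-up contrast multiplied by r. At r = .5 that is .05 and .07 SD; at r = .2 it is .02 and .03.

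**The case against.** - **Not named is not excluded.** A reader might infer that H1 will be analysed without its baseline value. The article does not support that: the covariate clause in H1 and the general statement on precision both leave room for it. What stands is that nothing is fixed for H1, whereas H2 and H4 are fixed.
- **The hypotheses differ.** H2 concerns reductions, which call for a baseline reference. H1 concerns the amount of treatment attended after randomisation, and an unadjusted follow-up comparison answers that validly. This is fair, and it makes adjustment a gain in efficiency. It does not explain the difference fully, because H4 is about functioning at follow-up and still adjusts.
- **The .5 is not a baseline correlation.** It would be easy to read the plan's .5 as r and quote the 40% reduction as the plan's own figure. The article states .5 for the repeated measurements, and in the H1 model those are the four follow-ups. Of the flagged patients who received no in-depth screening, 1060 were already in substance use treatment, so baseline counts among those enrolled may cluster near zero and r may be low. Being in treatment is not a listed exclusion criterion, so the counts need not all be zero.
- **Imbalance is not bias.** A reader might infer that chance differences in prior treatment bias H1. They do not: over repeated randomisations they are already part of the standard error, and they carry through only in proportion to r. Randomisation was also stratified by site, behavioral health consultant and severity. Given an observed imbalance, the covariate still removes the shift it causes.
- **Detail for the analysis plan.** Naming covariates is often left there. Here, though, the article itself specifies the baseline covariate for H2 and H4, so the difference lies in the text shown.

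**Conclusion.** The point holds as one of prespecification and possible precision. H1 alone among the mixed-model outcomes has no fixed baseline covariate, although its instruments are scheduled at baseline, and the choice stays open after the baseline comparison.

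The H1 analysis is not invalid, and the sample size is not undermined. The loss of precision is uncertain: from about 2% of variance at r = .1, through 6% at .2 and 14% at .3, to 40% only if r reaches .5. At that upper value the unadjusted standard error is 29% larger than the adjusted one (1/√.6 = 1.29). In the illicit-drug sub-group there is little power to regain at the planned d = .5. These figures rest on compound symmetry and on an r that the documents do not give. The case for closing the covariate choice does not depend on r.

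**What to change.** State in the H1 model that the baseline count of substance-use sessions outside the FQHC is entered as a covariate, in the same way as H4 ("the baseline response variable will be entered as a covariate in the model"). If baseline counts are mostly zero, add an any/none indicator, and decide this on counts pooled over both arms. Fix the wording before the groups are compared at baseline. If the omission was deliberate, give the reason instead.

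Before relying on the variable, check that the baseline look-back period matches the 90-day outcome window; the article does not state it.

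The cost is a sentence and one or two degrees of freedom. No new instrument or visit is needed, since Table 2 already schedules the measures at baseline.

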### Power for the primary hypotheses

Power analyses are based on the sub-group contrasts identified for each of the primary hypotheses. The analyses are based on a two sided alpha of .0125 (.05/4 outcome variables–number of treatment sessions attended, urinalysis-confirmed abstinence, days of self-reported drug use, and cost of acute care), an estimated correlation of .5 between the repeated measurements where applicable, and a 20 % attrition rate by month 12. Power calculations were based on Diggle, Heagerty, Liang, and Zeger [58] for the mixed effects models, Hedeker, Gibbons, and Waternaux [59] for the GEE models, and Cohen [60] for the cost-related hypotheses. With a sample size of 100 per condition in the illicit drug sub-group, we will have 80 % power to detect moderate effects of the intervention (*d* = .5) for the mixed effects models and cost-related analysis and 80 % power to detect a 20 % difference between the two groups for the GEE model. With a sample size of 200 per condition in the alcohol/marijuana sub-group, we will have 80 % power to detect smaller effects of the intervention (*d* = .25–.30) for the mixed effects models and cost-related analysis and 80 % power to detect smaller differences (13–15 %) between the two groups for the GEE model.

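### The outcome models do not commit to the severity stratum, and the H1 model does not commit to its baseline session count, so available precision is left to discretion

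*Protocol article*

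**What the plan says.** All references are to the protocol article.

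- **Design.** Under Data analysis: "we stratified based on site, behavioral health consultant, and drug or alcohol severity". Severity has three levels, taken from the AUDIT or DAST-10 score. The reason given is that severity has repeatedly been found to change how well brief intervention works.
- **H1 model.** Under Primary H1: "The model will include terms for intervention group, drug type (i.e., illicit drug or alcohol/marijuana), time, BHC/site, and relevant interactions". The sentence then ends with an open allowance for covariates judged necessary. Data analysis likewise says that some covariates will be considered for precision.
- **H2 and H4 models.** Both are described as similar to the H1 model, and both add the baseline response. For H2: "the baseline response variable (i.e., urine result or days drug use) will be entered as a covariate in the model". Primary H1 has no such statement.
- **Data available.** Table 2 lists the H1 instruments (NSMOS and patient charts) at baseline and at 3, 6, 9 and 12 months.
- **Contrasts.** They compare the arms within the illicit drug sub-group and within the alcohol/marijuana sub-group. No contrast by severity is named.

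**The concern.** The article lists its model terms, and the list does not match its own design rationale. Site and BHC are carried from the randomisation into the model. The third stratum, the only one justified as a known moderator, is not.

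When a prognostic stratum is left out of a linear model, its variance stays in the error term although the design has at least partly balanced it between arms. The reported standard error is then larger than it need be and power is lost.

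Severity matters particularly for H1, which counts sessions outside the health center. The intervention sections describe referral practice that differs by severity and by arm. Moderate patients are referred to community resources under BI/RT but generally not under BI/RT+, while severe patients are typically referred out under both. The arm effect on outside sessions may therefore differ by severity, and a contrast averaged over severity could hide that. The Discussion also promises to show which intensity suits which severity, but no model term is committed to that question.

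For H1 the baseline session count is usually the most obvious covariate to name, and the parallel models do name theirs.

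**Working it through.** **Inputs from Power for the primary hypotheses.** "The analyses are based on a two sided alpha of .0125"; "an estimated correlation of .5 between the repeated measurements where applicable"; "a 20 % attrition rate by month 12"; "With a sample size of 100 per condition in the illicit drug sub-group"; and 200 per condition for alcohol/marijuana. Attrition leaves 80 and 160 per condition. **Assumed:** R², the share of the variance of a participant's outcome averaged over visits that severity explains beyond the terms already in the model. The range shown is 5% to 20%.

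**1. The plan's own figure.** Critical value z = 2.498 (two-sided .0125); z for 80% power = 0.842; sum 3.339. The variance of a mean of four visits at correlation .5 is (1 + 3 × .5)/4 = .625. Detectable d = 3.339 × √(2 × .625/n).
- n = 200: d = .264
- n = 160: d = .295

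Both lie inside the stated .25–.30. The figure reproduces with no credit for covariates. For the illicit drug sub-group, n = 80 gives d = .417, so the stated d = .5 is conservative for a four-visit average.

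**2. Power gained by adding severity.** Adjusted power = Φ(3.339/√(1 − R²) − 2.498), for a contrast planned at 80%.

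| R² | Unadjusted SE relative to adjusted, 1/√(1 − R²) | Power when adjusted |
|---|---|---|
| .05 | 1.026 | 82.3% |
| .10 | 1.054 | 84.7% |
| .20 | 1.118 | 89.2% |

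**3. How conservative the unadjusted test would be.** Drug type was not a stratum, so severity is only partly balanced within each sub-group. Assume each sub-group is a constant fraction f of every stratum. The planned sizes give f = 200/600 = 1/3 (illicit drugs) and 400/600 = 2/3 (alcohol/marijuana). The true variance of the unadjusted estimate is then about (1 − f·R²) of what the model reports, and the actual type I error is 2 × [1 − Φ(2.498/√(1 − f·R²))].

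| Sub-group | R² = .10 | R² = .20 | Nominal |
|---|---|---|---|
| Illicit drugs (f = 1/3) | .0111 | .0097 | .0125 |
| Alcohol/marijuana (f = 2/3) | .0097 | .0073 | .0125 |

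Partial balance also lifts the unadjusted power slightly above 80%, to Φ(0.842/√(1 − f·R²)). At R² = .20 this is 80.8% (illicit drugs) and 81.7% (alcohol/marijuana). The gains in step 2 are therefore overstated by at most about 2 points over this range.

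**4. Baseline sessions in H1.** If baseline correlates r with each follow-up visit, the variance of the four-visit mean falls from .625 to .625 − r². At d = .30 and n = 160, power = Φ(.30/√(2 × (.625 − r²)/160) − 2.498).

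| r (assumed) | Residual variance | Power |
|---|---|---|
| 0 | .625 | 81.5% |
| .1 | .615 | 82.2% |
| .2 | .585 | 84.4% |
| .5 | .375 | 97.0% |

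The last row borrows the article's repeated-measures correlation. There the unadjusted SE is √(.625/.375) = 1.29 times the adjusted one. That is an upper illustration rather than an expectation: 1060 flagged patients already in substance use treatment received no in-depth screening (Screening and recruitment), so baseline sessions among those enrolled may be few and weakly predictive.

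**The case against.** The strongest reply is that nothing is excluded. The H1 sentence ends by allowing necessary covariates, Data analysis allows covariates for precision, and a condensed article may leave the full list to the protocol or analysis plan. This stands in part: a reader might infer that severity and baseline sessions are omitted, and the text supports only that they are not committed to. It does not dispose of the point. The article does list terms, carries over two strata and not the third, and states the baseline covariate for H2 and H4 but not H1. H3 names no covariates either, so the comparison holds only among H1, H2 and H4.

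The size of the gain is also open to challenge. R² is assumed, and what counts is the share added after drug type, BHC/site and, in H2 and H4, the baseline response. This stands. At 5% the gain is about 2 points of power.

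Three stronger readings are tempting and are not supported:

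- **A markedly conservative test.** Full balance on severity would give .0085 or .0052 at R² of 10% or 20%. The contrasts lie within drug-type sub-groups, where balance is partial, so those figures do not apply.
- **Adjustment for post-randomisation readiness.** Table 2 gives "Readiness to change and personal stress" the purpose of covariates and lists baseline and every follow-up. It does not say that follow-up values enter an outcome model. Repeated collection is not a plan to adjust for them.
- **Inflated standard errors in every model.** The argument is for the linear mixed models. The urine outcome uses a GEE whose link is not stated. With a logit link, leaving out a prognostic factor mainly moves the odds ratio toward the null.

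**Conclusion.** The point holds as a missed commitment. Severity is a randomisation stratum and a stated moderator, yet it is not a named term in the H1 model or in the models patterned on it. H1 does not name the baseline value that its sister models do.

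The consequence is lost precision in the linear models: about 2, 5 or 9 points of power at an added R² of 5%, 10% or 20%, starting from 80%. Any conservatism of the unadjusted test is mild: about .011 to .010 for illicit drugs and .010 to .007 for alcohol/marijuana at 10% to 20%, against .0125. These figures rest on the assumed R² and on sub-groups forming a constant share of each stratum. The benefit of baseline sessions ranges from negligible to large, depending on a correlation the article does not give.

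Leaving these terms out causes no bias in the linear-model contrasts and no inflated type I error. The stated power takes no credit for covariates, so it is not made wrong. This is a worthwhile improvement, not a threat to validity.

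**What to change.** Before outcomes are compared by arm, state in the analysis wording that:

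1. the three-level severity stratum enters the H1, H2 and H4 models as a fixed effect, beside BHC/site;
2. arm-by-severity is a pre-stated secondary moderator term, reported with its interval and kept separate from the primary drug-type contrasts;
3. the baseline 90-day session count enters the H1 model as a covariate, matching H2 and H4. If the baseline instrument uses another recall period, say which count is used.

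The cost is a sentence or two. Severity was recorded for randomisation and Table 2 lists the H1 instruments at baseline, so no new data are needed. The severity main effect uses two degrees of freedom and the arm interaction two more, which is negligible at these sample sizes. If baseline sessions turn out to be nearly all zero, the covariate will gain little and cost almost nothing.
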